## Appendix B: New York Heart Association (NYHA) Cardiac Classification

The NYHA classification system relates symptoms to everyday activities and the patient's quality of life.

| Class                | Symptoms                                                                                                                                                                  |
|----------------------|---------------------------------------------------------------------------------------------------------------------------------------------------------------------------|
| Class I (Mild)       | No limitation of physical activity. Ordinary physical activity does not cause undue fatigue, palpitation, or dyspnea (shortness of breath).                               |
| Class II (Mild)      | Slight limitation of physical activity. Comfortable at rest, but ordinary physical activity results in fatigue, palpitation, or dyspnea.                                  |
| Class III (Moderate) | Marked limitation of physical activity. Comfortable at rest, but less than ordinary activity causes fatigue, palpitation, or dyspnea.                                     |
| Class IV (Severe)    | Unable to carry out any physical activity without discomfort. Symptoms of cardiac insufficiency at rest. If any physical activity is undertaken, discomfort is increased. |

## **APPENDIX C: Correlative Science**

### **1. General**

The purpose of the correlative science studies is to explore if there are potential signals that may be predictive of activity of combined EGFR and VEGF inhibition. Samples will be based on prior archived biopsies (for patients that have both a biopsy from the primary tumor and site of metastases, both samples will be used) and serum samples at intermittent time points. The samples will not be used for genetic testing or for the generation of immortalized cell lines. Tumor blocks will be obtained from all patients in DLT finding phase and MTD phase of trial. Serum sample will only be drawn and required from patients treating during MTD phase.

The analyses of tumor blocks will be performed in the laboratory of Drs. [name] and [name]. The analyses of plasma markers and circulating endothelial cells were performed in the laboratory of [name].

Upon receiving the samples they will be re-labeled with a unique identifier. The code key will be kept in a password protected program only available to investigators in the clinical trial.

Tissue collection will consist of uncut paraffin embedded blocks that currently exist either in DFHCC institutions or in referring institutions. If a biopsy or resection has been performed at a non-DFHCC institution, tissue blocks will be requested from the referring institution. In this situation, a copy of the patient's informed consent form will be provided to the referring institution. Alternatively, if the pathology department at the referring institution will provide only unstained sections, 20 slides of 5 micron thickness. Any remaining samples and test samples, such as unstained slides will be retained at the testing laboratory until completion of the trial. All samples will be destroyed after a maximum of 10 years.

Serum samples will be drawn by an experienced phlebotomist or a research nurse as specific below.

It is not proposed that the analysis of results from a specific subject are made available routinely to either the subject or the treating physician, however, group results from this trial will be published.

### **2. Proposed markers of tumor tissue to test**

We will explore molecular alterations in tumor blocks in VEGF, CD31 (for microvessel density), EGFR, p21, p53, p-AKT1, MSI, Kras, and BRAF. In a recent report by our group of patients treated with gefitinib, irinotecan, 5-FU and leucovorin as initial chemotherapy for metastatic colorectal cancer, patients with tumors demonstrating p21 expression, combined p21 and p53 expression, and p-AKT1 expression (downstream

effectors of EGFR) had a lower likelihood of having a radiographic response to therapy. Mutations in *K-ras* may predict resistance to gefitinib in lung cancer.

We will also explore plasma VEGF and other angiogenesis cytokine levels (see below) prior to treatment and at 3 time points after treatment commences. Blood samples will be collected on day 1 prior to the start of therapy, on day 8, on day 22 and at week 9.

### 3. Methods for tumor tissue testing

*PCR and Sequencing KRAS and BRAF.* Tumor tissue (and normal tissue if applicable) will be reviewed and dissected from tissue sections obtained from the paraffin tissue blocks, and genomic DNA will be extracted using QIAmp DNA Mini Kit. For whole genome amplification (WGA), genomic DNA will be PCR-amplified using random 15-mer primers. *KRAS* and *BRAF* sequencing will be performed using Pyrosequencing technology as previously described by Ogino et al.

*Microsatellite Instability (MSI).* We determine MSI status by PCR of BAT25, BAT26 and BAT40 microsatellites as previously described. Tumors with either unstable BAT25 or BAT26 will be diagnosed as MSI-high. If no normal tissue is available, tumors that show two peaks in at least two microsatellites will be diagnosed as MSI-high.

*Immunohistochemical Analyses.* For EGFR immunohistochemistry, paraffin sections of CRC will be deparaffinized, incubated with 3% H2O2 (20 min) to block endogenous peroxidase, and then incubated with pepsin at 37°C (10 min). Protein block (Vector Laboratories, Burlingame, CA) (20 min) will be followed by application of primary anti-EGFR antibody (Zymed Laboratories, South San Francisco, CA) (dilution 1:100; overnight at 4°C). Then, secondary anti-mouse antibody (Vector Laboratories) was applied (20 min), avidin biotin complex will be added and sections visualized by diaminobenzidine (DAB) (5 min) and methyl-green counterstain. EGFR expression will be recorded as negative (0), weakly positive (1+), positive (2+), or strongly positive (3+). The extent of staining will also be recorded.

For phosphorylated AKT1 (p-AKT1) immunohistochemistry, antigen retrieval will be performed by incubating deparaffinized tissue sections in citrate buffer by a microwave at 92.8°C for 15 min and 30 min. Tissue sections will be then incubated with 3% H2O2 (30 min) to block endogenous peroxidase, and then incubated with protein block (Vector Laboratories) (30 min). Primary anti-p-AKT1 antibody (Cell Signaling, Beverly, MA) (dilution 1:50) was applied for overnight at 4°C. Then, secondary anti-rabbit antibody (Vector Laboratories) will be applied (30 min), avidin biotin complex will be added and sections visualized by DAB (5 min) and methyl-green counterstain. p-AKT1 expression was interpreted as negative or positive, using normal epithelial cells and lymphocytes as reference.

For p21 (CDKN1A/CIP1) and p27 (CDKN1B/KIP1) immunohistochemistry, antigen retrieval will be performed by incubating deparaffinized tissue sections in citrate buffer at

high power in a microwave for 30 min (in a pressure cooker) and 15 min, respectively. Tissue sections will then incubated with 3% H2O2 (10 min) to block endogenous peroxidase, and then incubated with protein block (Vector Laboratories) (10 min). Primary anti-p21 antibody (Pharmingen, San Diego, CA) (dilution 1:50) or anti-p27 antibody (Transduction Laboratories, San Diego, CA) (dilution 1:200) will be applied for 30 min at room temperature. Then, biotinylated secondary Multi-Link antibody (Biogenex, San Ramon, CA) will be applied (20 min), horse radish peroxidase avidin complex (Biogenex) will be added and sections visualized by DAB (30 sec) and methyl-green counterstain. p21 expression will be recorded as negative (< 10% of cells staining) or positive (≥ 10% of cells staining). and p27 expression will be recorded as negative (≤ 20% of cells staining) or positive (> 20% of cells staining).

We will assess for mutations in p53 (*TP53*) by immunohistochemistry. Methods for p53 immunohistochemistry were previously described. Only strong and unequivocal staining with ≥ 50% of cells staining will be interpreted as positive. Weak or staining in <50% of cells for p53 will be regarded as negative.

VEGF immunohistochemistry will be performed as previously described with polyclonal anti-VEGF (A-20, Santa Cruz Biotechnology) will be used at 1:100 dilution. For evaluation of tumor microvessel density (MVD), we will use an automated imaging system, Ariol 2.0 (Applied Imaging), and CD31 immunohistochemistry that positively stains vascular endothelial cells. CD31 immunohistochemistry will be performed as previously described with anti-CD31 (JC70; Dako), dilution 1:10. Individual microvessels will be counted in a single 250x field of a highly vascular tumor area excluding ulceration or granulation tissue. MVD in each tumor will be defined as the microvessel count of the field with the highest number of microvessels.

All immunohistochemical and molecular results will be interpreted as blinded from patients' identity and clinical outcomes data.

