### 2.3 EXPLORATORY

We will explore whether molecular alterations within tumor blocks in VEGF, CD31 (for microvessel density), EGFR, p21, p53, p-AKT1, MSI, K-ras, and BRAF with responsiveness to therapy to seek for any tissue biomarker to predict responsiveness or resistance to the combination under study. We will explore changes in serum VEGF and other angiogenesis cytokine markers before and after initiation of ZD6474. See Appendix C.

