### 3.3 EXPECTED NUMBER OF PATIENTS

The number of patients expected to enroll would be 3-34 (dependent on dose level obtained and whether an MTD will be tested).

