### 13 Statistical Considerations

This is a phase I study, initially with dose escalation of ZD6474 and then adding irinotecan. The study will likely accrue between 6 and 15 patients (before MTD testing) with the described dose escalation schema, though it could range from 3 to 34 patients. We expect accrual to be 2-3 patients / month (though this will vary during waiting periods to proceed to next dose level). If patients in dose levels 2-4 who have a DLT in the first 14 days (prior to initiation of irinotecan), the patient will not be counted towards the DLTs of that cohort and an additional patient will be substituted. For example, if one of the first 3 patients in dose level 4 have a DLT, that patient will not be calculated into the DLT tabulation for ZD6474,

cetuximab and irinotecan and an additional patient will be substitute in that spot. If this scenario occurs twice, the study will be held and the study team will reevaluate the ZD6474 / cetuximab toxicity profile. To ensure the toxicity at the MTD is acceptable and to further define any toxicity that may occur with this regimen, an additional 10 patients will be accrued at the MTD. The estimation of toxicity rate will be based on these 10 additional patients. With 10 patients, the 90% confidence bounds for any toxicity will be  $\pm 28\%$ . The probability of a dose level declared too toxic based on the true DLT rate is defined as such:

| True DLT Rate | Probability of declaring dose too toxic |
|---------------|-----------------------------------------|
| 20%           | 0.29                                    |
| 30%           | 0.51                                    |
| 40%           | 0.69                                    |
| 50%           | 0.83                                    |
| 60%           | 0.92                                    |

Response rate, progression-free survival and overall survival are secondary analyses. Each will be reported by dose level and at the MTD.

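### p21 staining is recorded only as negative or positive at 10% of cells; recording the percentage as well would cost almost nothing and preserve information if the link with response is graded

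*Protocol*

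**What the plan says.** The exploratory objective (section 2.3) is "to seek for any tissue biomarker to predict responsiveness or resistance to the combination under study". Appendix C, section 2 gives the rationale: in the group's earlier report, tumors expressing p21, among other markers, were less likely to respond.

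The recording rules are in Appendix C, section 3:

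- p21: "p21 expression will be recorded as negative (< 10% of cells staining) or positive", where positive means 10% of cells or more.
- p27: "p27 expression will be recorded as negative (≤ 20% of cells staining) or positive (> 20% of cells staining"). p27 is not in the marker lists of section 2.3 or Appendix C, section 2.
- EGFR: a four-level score from 0 to 3+, and then "The extent of staining will also be recorded".

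On numbers, section 3.3 says "The number of patients expected to enroll would be 3-34", and section 13 says "The study will likely accrue between 6 and 15 patients (before MTD testing"), with 10 more at the MTD. Tissue is sought from everyone: "Tumor blocks will be obtained from all patients in DLT finding phase and MTD phase of trial". The protocol names no test, significance level, effect size, p21 distribution or expected share of positive tumors for the marker analysis.

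**The concern.** The p21 sentence is a rule about what data are captured. The choice of test can be left to an analysis plan, but no analysis plan can analyze a percentage that was never written down. Recovering it later would mean re-reading slides, and Appendix C, section 1 keeps remaining and test samples only until the trial ends, with destruction of all samples after at most 10 years.

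The aim is to search for any predictive marker in a small trial. If response falls steadily as p21 staining rises, a two-level record treats a tumor with 12% of cells staining the same as one with 90%, and a real association is easier to miss. The EGFR rule shows that the plan keeps graded data where it wants them.

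Two other binary readings in the section are different. The p53 cut at 50% stands in for mutation status. The p-AKT1 call is made against normal reference cells, with no percentage cut behind it.

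**Working it through.** **Plan's own figure.** There is none for this analysis. The probabilities and confidence bounds in section 13 concern toxicity only.

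**Inputs from the protocol.** The maximum is 34 patients (section 3.3). Response rates of 23% (section 1.3) and 37% (section 1.6) are background figures for related regimens, not design assumptions. They give 34 × 0.23 = 7.8 and 34 × 0.37 = 12.6, so about 8 to 13 responders.

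**Assumed inputs.** Underlying staining is normal, with responders 1.0 SD lower. Tests are two-sided at 5%. Either 50% or 30% of tumors are positive. There are no ties at zero unless stated.

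**Step 1: approximation.** Cutting a normal marker at c, with a share p positive, has relative efficiency φ(c)² / [p(1 − p)].

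- p = 50%: 0.3989² / 0.25 = 0.64
- p = 30%: 0.58
- p = 10%: 0.34

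Power for the cut is Φ(√efficiency × (1.96 + z_power) − 1.96), where z_power belongs to the graded test. For a graded test with 80% power and p = 50%: 0.798 × (1.96 + 0.84) − 1.96 ≈ 0.28, so power is about 0.61, a loss of 19 points. If the graded test has 50% to 90% power and 10% to 90% of tumors are positive, the loss is about 15 to 43 points. If it has only 10% to 30% power, the loss is about 2 to 17 points.

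**Step 2: simulation at n = 34 and 1.0 SD.**

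| Share positive | Response | Cut, Fisher | Cut, chi-square | Percentage, rank test |
|---|---|---|---|---|
| 50% | 23% | 0.33 | 0.45 | 0.59 |
| 50% | 37% | 0.49 | 0.58 | 0.73 |
| 30% | 23% | 0.15 | 0.24 | 0.61 |
| 30% | 37% | 0.35 | 0.47 | 0.73 |

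Against chi-square the gain from the percentage is 14 to 15 points at 50% positive (0.59 − 0.45; 0.73 − 0.58) and 26 to 37 points at 30% positive (0.73 − 0.47; 0.61 − 0.24). Against Fisher it is 24 to 26 and 38 to 46 points. At 50% positive, 9 to 12 points of the Fisher gap come from Fisher's conservatism, not from the cut: under no association Fisher rejects only 2% to 3% of the time, against 4% to 5% for the rank test.

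**Step 3: where the loss shrinks (n = 34).**

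- *Weak effect* (odds ratio 1.5 per SD): the loss is about 5 to 13 points against Fisher and −1 to 11 against chi-square. The graded test itself has only about 12% to 19% power.
- *Step in response exactly at the cut* (30% response): rank minus Fisher is +3 to −22 points, so the binary test is usually equal or better.
- *Half the tumors positive and the negative half all tied at zero*: the gain over chi-square is about −2 to +5 points.

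**The case against.** The strongest case on the other side has four parts.

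- **The p21 evidence is categorical.** Appendix C, section 2 reports on tumors that do or do not express p21. Testing that signal with a fixed definition is legitimate replication. This stands, and is why the cut should stay.
- **The cut is not data-driven.** It is fixed in advance and read blind to outcome, so there is no cut-point bias. This also stands.
- **The text does not say that the percentage is thrown away.** That is correct. Reading the rule as category only is an inference, though a fair one: the EGFR rule adds a sentence keeping the extent of staining, and the p21 and p27 rules do not.
- **The choice of comparison belongs in an analysis plan.** This largely stands. Only the data field has to be settled in the protocol.

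A reader might infer three stronger things. The first is a definite loss, such as 15 to 45 points. The documents do not support a fixed figure, because the test, effect size, share positive and distribution are all unstated; depending on them, the result runs from a gain for the binary test to a loss above 70 points. The second is that the exploratory objective would fail. p21 is one of nine listed tissue markers, and nothing commits the team to call a non-significant marker non-predictive. The third is that the cut should be replaced as the main analysis. If the relation is a step at the cut, that would usually be no better and could be worse.

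**Conclusion.** The point holds as a minor improvement. The protocol fixes a two-level record for p21, and for p27, when a graded value has to be judged anyway. If the association with response is graded and of moderate size or larger, the category alone loses useful power: roughly 14 to 37 points against an uncorrected chi-square test under the step 2 assumptions, and more against Fisher. The loss is small for weak effects and little or none for a step at the cut or when the negative half of tumors do not stain.

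The figure of 34 is the ceiling of the stated range. With fewer patients or modest effects, the graded test is also underpowered, so the percentage would not make this a well-powered analysis. Dose level 1 also receives no irinotecan, so a comparison pooled over dose levels mixes regimens on either scale. The case for recording both forms does not depend on which shape is true, because having both covers either. The MTD and the secondary endpoints are not affected.

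**What to change.** In Appendix C, section 3, change the p21 sentence to say that the percentage of tumor cells staining (0 to 100%) will be recorded together with the category at the existing 10% cut. Do the same for p27 at its 20% cut if p27 is kept.

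Add, here or in the analysis plan, a rank-based comparison of the percentage between responders and non-responders, such as a Wilcoxon test. Place it beside the prespecified negative/positive comparison, which stays for comparability with the group's earlier report. Any statement about power should give its assumptions.

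The cost is one sentence and one data field per marker. No extra stain, sample or reader is needed. The downside is some reader variability in the percentage, which is another reason to keep the category.

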#### 4. Serum Marker Studies

To measure numerous biomarkers simultaneously with exceptional sensitivity but only small amount (~10µl) of plasma proteins, the MSD (Meso Scale Discovery, Maryland) platform will be used. MSD technology utilizes electrochemiluminescence detection to detect binding events on patterned arrays. By customizing the Multi-Array, up to 10 plasma molecules can be simultaneously tested (Willett et al., JCO 2005). We will collect blood samples from the patients before and during the course of treatment (see below), and use MSD technology to measure tumstatin, as well as other well established biomarkers such as VEGF-A, -D, sVEGFRs, PlGF, EGF, TGF-α, PDGF-AA, PDGF-AB, PDGF-BB, angiopoietin-1, thrombospondin-1 and IL-8. The level of these markers during treatment will be compared to the baseline level.

##### 4.1 Sample Collection Time Points

Blood samples will be obtained for protein analysis of potential biomarkers for anti-angiogenic therapy at the following time points:

- Prior to starting therapy on day 1 of cycle 1
- Days +8, 15, 22
- Day 1 of start of every other cycle until patient goes off study

#### 4.2 Supplies

##### **Blood collection supplies (needed for each time point sample)**

- Acceptable Tubes
  - SARSTEDT Monovette® EDTA KE (9 ml), Part # 02.1333.001 **or**
  - Becton-Dickinson Vacutainer™ K2E (10 ml), Part # 367525 **or**
  - Greiner Bio-One Vacuette® K3E EDTA K3 (9 ml), Part 455036
- Blood tubes must be gently inverted several times after collection to ensure thorough mixing of EDTA with the sample to prevent clotting.
- **Glass tubes MUST NOT be used** as they may break during transport and freeze-thaw cycles.
- **Heparin must not be used as an** anticoagulant as it may interfere with downstream genotyping methodology.
- Ten (10) red-labeled Nalgene cryovials

#### 4.3 Sample Labels

For each blood collection, prepare two red (for plasma) labels each printed with Study-No., patient ID, initials and day/time of sample collection (24-hour clock format, *i.e.*, 6:30 pm = 18:30). Alternatively, purple screw caps can be used to color code the vials.

For one timepoint per patient, label one tube as “do not discard” (for the purpose of extracting genomic DNA in the future)

#### 4.4 Collection and Handling

##### **Blood (Plasma) collection**

- Collect ~ 10 ml of blood into any of the tubes listed 4.2. The tubes must be pre-cooled in an ice bath.
- Gently invert five to six times to ensure adequate mixing and prevent coagulation.
- Cool the tubes immediately in an ice bath.
- Centrifuge at 2000 RPM for 20 minutes at 4 degrees C without break
- Plasma is pipetted in ten 4-5 ml aliquots and frozen at -80 °C until shipped (on dry ice)
- Save and freeze the red cell layer at -80 °C from one timepoint per patient (otherwise disregard red cell layer)

**5. Circulating Endothelial Cells Assay**

Targeting angiogenic vessels requires adequate methods for the assessment of the biologic effect of various new drugs developed to control cancer progression. Tumor angiogenesis is evaluated mainly by measuring microvessel density (MVD) in biopsy specimens using immunohistochemistry. Predicting and/or assessing accurately the efficacy of antiangiogenic therapies by this method is hampered by the heterogeneity of tumors, and by the difficulty to obtain specimens at multiple time points during treatments. On the other hand, the number of circulating endothelial cells (CECs) – measured by flow cytometry – is significantly increased in the peripheral blood of untreated lymphoma and breast cancer patients (Mancuso et al. 2001). Furthermore it has been shown that in lymphoma patients achieving complete remission after chemotherapy, the number of CECs was reduced to the values observed in healthy controls, and activated CECs were found to decrease in breast cancer patients evaluated before and after quadrantectomy. The strong correlation observed between the number of CECs and tumor volume indicates that the number of CECs increase with tumor progression (Monestiroli et al. 2001). The evaluation of CEC kinetics and viability before and after drug therapy demonstrated that in control animals, most CECs seem to have initiated an apoptotic program, whereas CEC viability is markedly improved in tumor-bearing mice. Moreover, a correlation has been observed between CEC and plasma levels of human VEGF (produced by tumor cells), suggesting that the antiapoptotic properties of VEGF may also play a role in determining the number of CECs in tumor-bearing mice. The increase in CECs has been attributed to shedding from tumor vessels or from distant sites and uninvolved vessels that are activated by cytokines produced by the tumor (such as from the bone marrow, Ref (Rafii et al. 2002). We have recently characterized the phenotype and kinetics of CECs in peripheral blood of rectal cancer patients during VEGF-blockade (Duda et al., JCO 2006).

We have recently shown in humans that this method may be used for evaluation of the early response to VEGF blockade in patients with rectal carcinoma (Willett et al. 2004 and 2005). Specifically, a decrease in both viable CECs and progenitor cell number was noted 3 days after administration of the VEGF-specific antibody, bevacizumab.

This decrease was sustained at day 12 (which is close to the half-life of bevacizumab in circulation) only in patients who received the high-dose of 10 mg/kg bevacizumab. This difference between the high- and low-dose of bevacizumab may have been caused by the significant increase in plasma VEGF and PlGF in all patients at both day 3 and day 12 compared to pre-treatment (Willett et al., 2005).

